**Discussion:**

Our working hypothesis is that radiographic examination would actually exert little influence on patient-centered outcomes, and visual inspection would be enough as diagnostic strategy for caries detection in primary teeth.

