#### Sample size

The sample size calculation was based on the occurrence of the primary outcome: number of dental surfaces of primary molars with operative needs during the follow-ups and the incidence data. Considering operative needs, we observed a mean of 17.6 surfaces with new caries lesions after 2 years [31], approximately 10 % restoration failure of occlusal or occluso-proximal restorations in 2 years [32], 0.08 extracted teeth in 2 years, with 0.2 surfaces [33] and 0.3 pain episodes in 2 years, with one surface [33].

Therefore, a mean of 19 surfaces with treatment need in the visual inspection alone group is expected. A difference of five surfaces with treatment need in the visual plus radiographic method group was considered as a minimally clinically important difference. The standard deviation values expected for visual and visual plus radiographic groups were 15 and 10, respectively. Therefore, using a two-tailed test and considering a significance level of 5 % and 80 % power, the minimum sample size of children calculated was 103 per group. Anticipating an attrition rate of 80 %, the final minimum sample size was 250 children for the entire study.

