#### Statistical methods

For comparing the outcomes between the two groups, Student’s *t* test and Poisson regression analysis will be performed. With regard to the impact of Oral Health on quality of life, differences in the final and baseline scores will be compared between the groups through Student’s *t* test or the Mann–Whitney test, depending on the normality of the data distribution.

Multivariate analysis will be conducted to investigate the influence of the radiographic examination on treatment decision. Time and treatment cost will be compared by Student’s *t* test. An incremental cost-efficacy ratio will be used to compare the economic impact of both diagnostic strategies, considering both the initial examination and possible treatment and re-treatments during the study. The quality-adjusted life year (QUALY) will be also calculated in order to estimate the ratio of cost saved/spent by the use of the proposed diagnostic strategy. For all analyses, the level of significance will be set at 5 %.

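### The planned joint cost-effect comparison is a ratio whose denominator the trial expects to be small, so on its own it would often be uninterpretable; incremental net benefit should carry the inference

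*Protocol article*

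**What the plan says.** The Statistical methods section of the protocol article plans three economic analyses.

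- Costs on their own: "Time and treatment cost will be compared by Student’s *t* test".
- Cost and efficacy jointly: "An incremental cost-efficacy ratio will be used to compare the economic impact of both diagnostic strategies". Costs are to include the initial examination and any later treatment and re-treatment. The efficacy unit in the denominator is not named.
- Quality of life: "The quality-adjusted life year (QUALY) will be also calculated in order to estimate the ratio of cost saved/spent".

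The same section compares the clinical outcomes between arms by t test and Poisson regression. Cost-efficacy is listed as a secondary outcome under Outcomes.

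The Discussion paragraph of the Abstract gives the expected result: "Our working hypothesis is that radiographic examination would actually exert little influence on patient-centered outcomes". The Sample size section, by contrast, sizes the trial for a difference of five surfaces: "A difference of five surfaces with treatment need in the visual plus radiographic method group was considered as a minimally clinically important difference".

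**The concern.** An incremental ratio is the cost difference divided by the efficacy difference. When the true efficacy difference is small relative to its standard error, chance in the denominator largely determines the size of the ratio and often its sign.

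The sign is also ambiguous. A negative ratio arises if radiographs are cheaper and better, and equally if they are dearer and worse. The number alone cannot separate the best result from the worst.

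The Background makes the cost of unnecessary operative treatment part of the rationale, and the main Discussion hopes to overturn guideline advice on bitewings. If the working hypothesis is true, the trial could publish a large cost per surface, of either sign, that mostly reflects noise.

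**Working it through.** **Inputs from the Sample size section.** "The standard deviation values expected for visual and visual plus radiographic groups were 15 and 10, respectively"; 103 children per group; difference of 5 surfaces; two-sided 5%; 80% power.

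**Assumptions.** Efficacy is the primary outcome, in surfaces with treatment need. Estimates are approximately normal. The protocol does not quantify little influence; I take 0 to 2 surfaces, well below the stated minimally important difference of 5.

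**Step 1: reproduce the plan's figure.** n per group = (15² + 10²) × (1.960 + 0.842)² / 5² = 325 × 7.849 / 25 = 102.04, rounded up to 103. This agrees with the protocol.

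**Step 2: precision of the efficacy difference.** Let dE be surfaces averted by adding radiographs and dC the extra cost. SE(dE) = √(325/103) = 1.776 surfaces.

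**Step 3: when the ratio has a bounded interval.** The Fieller 95% set contains every R for which

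(dC − R·dE)² ≤ 1.96² × [Var(dC) − 2R·Cov(dC, dE) + R²·Var(dE)].

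The set is a bounded interval only if dE² − 1.96²·Var(dE) > 0, that is, if |dE|/SE(dE) > 1.96. So whenever the efficacy difference is not significant at two-sided 5%, the ratio has no bounded 95% interval. This condition does not involve the costs or their correlation with effect.

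**Step 4: how often that happens.** With true difference d:

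- P(bounded) = [1 − Φ(1.96 − d/SE)] + Φ(−1.96 − d/SE)
- P(dE estimated below zero) = Φ(−d/SE)

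Example at d = 1: d/SE = 0.563, and P(bounded) = 0.087.

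| True difference (surfaces) | No bounded 95% interval, 103 per group | Same, 125 per group | Efficacy estimate below zero, 103 per group |
|---|---|---|---|
| 0 | 95.0% | 95.0% | 50% |
| 0.5 | 94.1% | 93.9% | 39% |
| 1 | 91.3% | 90.5% | 29% |
| 2 | 79.7% | 76.3% | 13% |
| 5 (design value) | 19.6% | 12.7% | 0.2% |

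The 125 column takes all 250 children as evaluable (SE = √(325/125) = 1.612). Full retention changes little in the range of interest.

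**Step 5: sign of the ratio.** This depends on cost as well. Simulations (200,000 replicates, 103 per group) used assumed cost differences in cost-SD units and assumed correlations, with fewer surfaces in need going with lower cost. With a clear cost difference (0.5 SD), the ratio was positive in about 50%, 71% and 87% of trials at true differences of 0, 1 and 2 surfaces. With zero effect, a cost difference of 0 or 0.2 SD and correlation 0.5 to 0.8, the positive share was 21% to 45%.

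**Step 6: the alternative.** Incremental net benefit at a value λ per surface averted is λ·dE − dC, with variance λ²·Var(dE) + Var(dC) − 2λ·Cov(dE, dC). It is linear in the two differences, so its interval is bounded for any dE, including zero.

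**The case against.** The strongest reply is that the economic comparison does not depend on this ratio alone. Costs are tested directly and outcomes are compared between arms, so the claim that radiographs cost more for no gain can be examined in its two parts. That stands. A reader might infer that the whole economic conclusion rests on the ratio, and the documents do not support that. The separate tests still do not combine cost with effect, and the QALY analysis is again described as a ratio.

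A reader might also infer that the ratio will fail in 95% of trials with a sign no better than a coin toss. Those are limits at a true difference of exactly zero. The protocol expects little influence, not none, and the ratio performs acceptably at the design value. An even split in sign also requires either a clear cost difference or no correlation between cost and effect. Since costs include re-treatment, correlation is plausible.

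Finally, the article does not say how the ratio's uncertainty will be shown. Cost-effect planes and acceptability curves are commonly left to an analysis plan, so that silence is not counted here. The point concerns the measure that the article does choose.

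**Conclusion.** The point holds as a limited one about a secondary outcome. Over true differences of 0 to 2 surfaces, the planned ratio would lack a bounded 95% interval in roughly 95% to 80% of trials. A trial with a real benefit of 1 or 2 surfaces would estimate it with the wrong sign in 29% or 13% of cases. At the 5 surfaces used for sizing, the interval is unbounded in only 20%.

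The 95% at zero effect follows from the 5% level alone. The other figures rest on the planning SDs and on taking surfaces with treatment need as the efficacy unit. The simulated sign frequencies rest on assumed costs and correlations and serve only as illustration.

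**What to change.** In Statistical methods, name the efficacy unit and make incremental net benefit (λ × surfaces averted − extra cost) the inferential cost-effect comparison, with a 95% confidence interval over a range of λ fixed in advance. Estimate it from each child's own paired cost and effect, so that their correlation is kept. Report with it the cost difference and the effect difference, each with a confidence interval, and the cost-effect plane. Keep the incremental ratio as a descriptive figure, shown whether or not the efficacy difference is significant, so that its reporting does not depend on the result.

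The cost is a change of wording and some extra analysis. Visits, procedure times and materials are already to be recorded, and no further children are needed. The drawbacks are that the result is a curve over λ instead of one number, and that the investigators must choose and justify the range of λ, for which the article gives no value.

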### Monitoring

#### Data monitoring

As adverse events related to the detection of caries lesions and dental treatments are unlikely, no Data Monitoring Committee will be established, and independent oversight of trial data collection, management and analysis will be undertaken by one author ([name]). The chief investigator ([name]) has overall responsibility for the study and is custodian of the data.

#### Harms

It is unlikely that our procedures will result in any adverse effects beyond those listed as trial outcomes. These effects are usually expected in any conventional dental treatment performed in pediatric dentistry clinical practice.

#### Auditing

Data entered will be subjected weekly to audit by the coordinator, and data queries will be raised as necessary. Any discrepancies detected will be corrected and systematically registered.

### Ethics and dissemination

#### Research ethics approval

The present protocol was submitted and approved by the Ethical Committee of the School of Dentistry, University of São Paulo on 25 May 2012.

#### Consent or assent

The participants’ parents or guardians will receive and sign an informed consent prior to the child being included in the research. Only children whose parents sign the consent will participate in the study.

#### Confidentiality

Participant confidentiality will be ensured using identification code numbers. Participant identifiable information will be stored in locked filing cabinets in a secure room. Medical information may be given only to the dentist’s team.

#### Access to data

Data generated from this trial will be available for inspection by request to the coordinator.

#### Ancillary and post-trial care

After completing the study, participants will continue to receive dental treatments, if needed, in our dental clinics.

#### Dissemination policy

Results will be reported in full through peer-reviewed journals, patient newsletters and a website.

## Discussion

We expect this study to provide the best scientific evidence for defining better diagnostic strategies for use in detecting caries in primary teeth. Considering the research architecture in diagnosis [34], the diagnostic studies have basic designs with increasing level of evidence for answering four basic questions in diagnostic research. The first three basic questions are answered through cross-sectional studies for method validation. Studies that address Phase 3 questions are performed to test the method in the target populations selected, consecutively or randomly, reducing the chance of selection bias, which may overestimate the performance of the diagnostic methods [35]. Several cross-sectional studies of accuracy have been published evaluating different methods of caries detection [36–38]. Nevertheless, we observed that most studies are lacking in the evaluation of clinically relevant aspects or patient-centered outcomes [39].

We observed in a recent published study that the additional tests do not bring great benefits to detect carious lesions in primary molars [12]. Since the introduction of selection bias was minimized in this study, strong evidence exists with respect to the detection of caries in primary teeth.

However, randomized clinical trials evaluating relevant outcomes for patients (Phase 4 questions) represent a higher degree of evidence in diagnostic research. This type of study is conducted to evaluate if patients who undergo a diagnostic method fare better than untested patients [34]. As an example, we can cite the issue of mammography for breast cancer detection. The validity of mammography has been confirmed by cross-sectional studies that perform the biopsy as the gold standard [40]. However, it is known that the real benefit of performing mammography as a screening test in women between 40 and 50 years of age is small. This observation is because the test would prevent death from breast cancer in less than 0.01 % of women under age 50 who undergo screening. Considering the problems of unnecessary treatment due to false-positive results, stress caused by the diagnosis of women who do not die from this disease (correct and incorrect diagnoses) and other problems, the risks outweigh the benefits of mammography in this age group [41]. This type of results can be only evaluated in randomized clinical trials because the validity studies do not deal with this aspect.

Until now, however, no randomized clinical trial was conducted to evaluate caries diagnosis strategies. With the expected results, we aim to achieve the refutation of the recommendation to conduct bitewing radiographs for detecting caries lesions, even in children without signs or symptoms, which is present in all protocols of clinical procedures worldwide. On the other hand, in case of favorable results obtained with the experimental group, we will confirm the benefits of strategies of caries detection advised by those clinical guidelines. To the best of our knowledge, this is the first randomized clinical trial to evaluate diagnostic strategies for diseases related to the oral cavity, considering the whole playing field of dentistry.

## Trial status

This is an ongoing trial, which is still recruiting participants at this moment. Figure 2 presents the CARDEC trial logotype. The CARDEC collaborative group represents all persons involved at this trial or in other studies that are been conducted and are nested in the CARDEC-01 trial. The group is formed by researchers, dentists, graduate and undergraduate students and technicians. The detailed roles of each member and respective affiliations are described in Additional file 2.

**Fig. 2 Fig2:**
[figure not shown]
CARDEC trial logotype

At the time of the submission of this manuscript, 225 participants had been included. Final results are expected by the beginning of 2018.

## Abbreviations

CARDEC: Caries Detection in Children
ICDAS: International Caries Detection and Assessment System
